## **Study population**

### **7.1.1 Subject population**

Patients, between 18 and 90 years, will be included in the study, who are scheduled to receiving a cochlear implant and who are willing to participate in the study.

### **7.1.2 Inclusion criteria**

- Patients between 18 and 90 years receiving a cochlear implant and who are willing to participate in the study.

### **7.1.3 Exclusion criteria**

- Patients younger than 18 years
- Patients who receive cortisone regularly or receive cortisone i.v. or p.o. preoperatively
- Patients with contraindications against the administration of Volon® A

### **7.1.4 Females of childbearing potential**

- Females of childbearing potential will be included in the study, if birth control is carried out (hormonal contraception, intrauterine or barrier contraception) or a pregnancy can be ruled out completely.

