**TABLE 1. VISIT AND ASSESSMENT SCHEDULE**

|                                         |          | Screening | Treatment     |                                    | Sampling | Follow Up |           |                  |
|-----------------------------------------|----------|-----------|---------------|------------------------------------|----------|-----------|-----------|------------------|
|                                         | Duration |           | 1 day         |                                    | 1 day    | 1 week    |           |                  |
| Visits                                  | Number   | 1         | 2             | 3                                  | 4        | 5         | 6         | 7                |
|                                         | Name     | Screening | Randomization | Application                        | Sampling | Control 1 | Control 2 | Control 3        |
|                                         | Time     |           | day 0         | day 0 (gr. 1+2)
day 1 (gr. 3+4) | day 1    | day 2     | day 3     | 1 week
+/- 2d |
| Informed Consent                        |          | x         |               |                                    |          |           |           |                  |
| Inclusion / Exclusion Criteria          |          | x         | x             |                                    |          |           |           |                  |
| Medical History                         |          | x         | x             |                                    |          |           |           |                  |
| Concomitant medication                  |          | x         | x             |                                    |          |           |           |                  |
| ENT Status                              |          | x         | x             |                                    |          |           |           |                  |
| Ear microscopy                          |          | x         | x             | x                                  |          | x         |           | x                |
| Body weight and height                  |          |           | x             |                                    |          |           |           |                  |
| Puretonaudiogramm                       |          | x         | x             |                                    |          | x         |           |                  |

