## **8. METHODOLOGY**

At the department of the Medical University of Vienna patients routinely receive intratympanic application of triamcinolone acetonide.

1 mL suspension containing 10mg (Groups 1 and 3) or 40mg (Groups 2 and 4) of triamcinolone acetonide is applied intratympanically via a 25G (0.50x90mm, 3.50 IN) needle after local anesthesia with xylocaine spray (10mg/Puff).

During the cochlear implant surgery, the cochlea is entered mostly via round window approach. Alternatively, if the round window cannot be identified, a cochleostomy is performed. After entering the cochlea, about 20µL of perilymph are sampled using a sterile disposable aspirator with a diameter of 0.4mm. A sterile insulin syringe is used to aspirate the perilymph. The perilymph sampling method has been performed similarly in other studies [2, 10].

Simultaneously a blood sample of 4ml is drawn in a heparin blood tube with a standard butterfly needle.

The sample of perilymph is stored in an eppendorf vial (volume 0,2ml) and frozen to approx. -80°.

The blood sample is centrifuged at 3000g, 20°C for 3 minutes at. The plasma is removed and stored in eppendorf vials (volume 2ml) and also frozen to approx.-80°. Both vials will be labeled with the patient number. Patients will be numbered with a randomly assigned three-digit number.

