### 9.1.6 Pregnancy

Any pregnancy that occurs during study participation must be reported to the Investigator/sponsor. To ensure subject safety, each pregnancy must be reported to the Sponsor immediately. The pregnancy must be followed up to determine outcome (including premature termination) and status of mother and child. Pregnancy complications and

elective terminations for medical reasons must be reported as an AE or SAE. Spontaneous abortions must be reported as an SAE.

Any SAE occurring in association with a pregnancy brought to the Investigator's attention after the subject has completed the study and considered by the Investigator as possibly related to the investigational product, must be promptly reported to the Investigator/sponsor. In addition, the Investigator must attempt to collect pregnancy information on any female partners of male study subjects who become pregnant while the subject is enrolled in the study. Pregnancy information must be reported to the Investigator/sponsor as described above.

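### Section 7.1.4 lets contraception stand in for establishing pregnancy status, and no pregnancy check is scheduled before dosing, so an unrecognised pregnancy is not caught

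*Protocol*

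**What the plan says.** Section 7.1.4 of the protocol gives the only rule on childbearing. Its first route reads "Females of childbearing potential will be included in the study, if birth control is carried out", followed by a bracket of accepted methods. Its second route is attached with an or: "barrier contraception) or a pregnancy can be ruled out completely".

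The inclusion criterion in section 7.1.2 covers only age, implantation and willingness: "Patients between 18 and 90 years receiving a cochlear implant and who are willing to participate in the study". The exclusion criteria in section 7.1.3 and in the synopsis do not name pregnancy. The one clause that could reach it is general: "Patients with contraindications against the administration of Volon® A". The protocol does not list those contraindications; section 8.1 refers to the investigator's brochure for drug information. The synopsis has no childbearing rule.

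Table 1 has a row for "Inclusion / Exclusion Criteria", ticked at Visit 1 (screening) and Visit 2 (randomisation, day 0). It has no row for a pregnancy check. Section 8.5.2 describes a second evaluation of the same criteria on day 0 and no further procedure.

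Section 9.1.6 deals with pregnancies arising during participation. It says that "each pregnancy must be reported to the Sponsor immediately" and requires follow-up to outcome for mother and child.

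**The concern.** The drug is given once (section 8.1.1), and each patient's active phase lasts at most nine days (section 7.1.5). For exposure in pregnancy, what counts is whether the woman is pregnant on the day of application. Use of contraception does not settle that, and section 7.1.4 sets no minimum period of prior use.

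The rule therefore accepts, as full evidence of eligibility, something that does not answer the question behind it. Section 9.1.6 shows that the protocol regards pregnancy as a safety matter, yet nothing in the schedule looks for it before dosing. At stake is the safety of a participant with an early pregnancy that nobody has recognised, and of the fetus. The scientific results are not at stake.

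**Working it through.** No arithmetic applies. The check is one of logic and of what is scheduled when.

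**1. The rule as a logical condition.** Let C mean that an accepted contraceptive method is used, and P that pregnancy has been ruled out. Section 7.1.4 includes a woman if C or P holds.

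- C yes, P yes: included.
- C no, P yes: included.
- C yes, P no: included.
- C no, P no: not included.

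The third case is the gap: she is admitted although her pregnancy status has not been established.

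**2. Whether another criterion closes the third case.** Section 7.1.2 does not bear on pregnancy. Of the exclusions in section 7.1.3, age and cortisone use are irrelevant. The contraindication clause could apply if the product information lists pregnancy, which the protocol does not say. Even then it works only on what the investigator knows, so an unrecognised pregnancy passes.

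**3. Whether a scheduled procedure closes it.** The rows of Table 1 are consent, eligibility criteria, medical history, concomitant medication, ENT status, ear microscopy, weight and height, audiogram, drug application, perilymph sample, blood sample and adverse events. None is a pregnancy check. The day 0 re-evaluation in section 8.5.2 applies the same criteria again, so a woman in the third case passes twice.

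**4. Whether the blood sample could serve.** Section 8 says of the moment of perilymph sampling: "Simultaneously a blood sample of 4ml is drawn in a heparin blood tube with a standard butterfly needle". In Table 1 this belongs to Visit 4, after the application at Visit 3. Under section 7 the interval from application to sampling is 20 to 24 hours in groups 1 and 2, and 1 to 2 hours in groups 3 and 4. In every randomised group the sample follows the dose, and it is taken to measure drug level. It cannot inform eligibility.

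**5. Whether section 9.1.6 closes it.** That section sets reporting and follow-up duties once a pregnancy is known. It contains no step for detecting one before application.

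**6. The second route.** It sets a demanding standard, complete exclusion of pregnancy, without naming a method in section 7.1.4, section 8.5.2 or Table 1.

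**The case against.** The strongest reply is that the gap is narrower than it looks, and much of that reply stands.

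- **The contraindication exclusion.** A reader might infer that any pregnant woman can satisfy all the criteria. The document does not support that. Section 7.1.3 may already exclude a known pregnancy, and whether it does turns on product information that is not shown. The point holds for an unrecognised pregnancy in a woman who enters through the contraception route.
- **Routine care.** Sections 7, 7.1.6 and 8 say that the department gives intratympanic triamcinolone routinely before implantation, so similar exposure could occur outside the trial. This weakens any claim that the trial creates the exposure. It does not remove the point, because the trial assigns dose and timing and has chosen to write its own childbearing rule.
- **Other checks.** A reader might infer that the protocol makes it impossible to rule out pregnancy. It does not. Medical history is taken at Visits 1 and 2, preoperative work-up may include a test, and nothing forbids one. But the protocol neither requires nor cites such a check, and the contraception route makes it unnecessary for eligibility.
- **Pregnancy follow-up.** A reader might infer that a pregnancy already present at enrolment would set off the duties in section 9.1.6. That section opens with pregnancies occurring during participation, so whether an earlier conception is covered is unclear.

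**Conclusion.** The point holds in limited form. As written, section 7.1.4 admits a woman using contraception without her pregnancy status being established, and no other criterion or scheduled procedure would reveal an unrecognised pregnancy before application. This is a fault in a stated eligibility rule and goes beyond an unspecified detail.

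The number of women concerned is not in the document. One could assume that 10% to 30% of the 40 randomised patients are women of childbearing potential, which gives 0.10 × 40 = 4 to 0.30 × 40 = 12. That share is an assumption, the count leaves out Group 5 of the synopsis, and it measures the wrong thing: the gap concerns only those who enter through contraception and are unknowingly pregnant. That number is likely very small.

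No endpoint, sample size, power figure or analysis is affected. The case for acting is participant safety at trivial cost. It rests on the text of section 7.1.4, Table 1 and section 8.5.2, and on no assumption about what the product information says.

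**What to change.** Reconcile the synopsis criteria, Table 1 and sections 7.1.3, 7.1.4, 8.5.2 and 9.1.6 so that:

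- contraception is not a substitute for establishing pregnancy status;
- the criteria and the visit schedule state how that status is established, before randomisation and drug application, for every woman of childbearing potential;
- the synopsis and the exclusion list agree with section 7.1.4 on pregnancy, and section 9.1.6 makes clear whether it covers a pregnancy that began before enrolment.

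The method is for the sponsor to choose; an existing preoperative result could serve. The cost is a short amendment, a minor added burden for a few women and an occasional screen failure.

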### **7.1.5 Study duration**

- Patients will be recruited over a time period of 2 years. The active phase of each patient will last for up to 9 days.

### **7.1.6 Withdrawal and replacement of subjects**

#### **Criteria for withdrawal**

Subjects may prematurely discontinue from the study at any time.

Subjects must be withdrawn under the following circumstances:

- at their own request
- if the Investigator feels it would not be in the best interest of the subject to continue

- if the subject violates conditions laid out in the consent form or disregards instructions by the study personal

In all cases, the reason why subjects are withdrawn must be recorded in detail in the CRF and in the subject's medical records. Should the study be discontinued prematurely, all study materials (completed, partially completed and empty CRFs) will be retained.

### **Follow-up of patients withdrawn from the study**

Patients routinely receive intratympanic Triamcinolone acetonide. The study only consists of the calculation of Triamcinolone acetonide concentration in the perilymph and blood. Patients will be asked for adverse events at routine post-operative follow-up visits. No further follow up visits are necessary or planned within this study.

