## 7. STUDY DESIGN

At the ENT department of the university hospital Vienna (AKH Wien) patients are treated with intratympanic triamcinolone acetonide before cochlea implantation to reduce inflammation and in some cases to protect residual hearing. Triamcinolone acetonide levels in cochlear perilymph will be evaluated in an open prospective clinical study. Patients scheduled for cochlear implant surgery between 18 and 90 years will be included. Patients who are treated with steroids preoperatively will be excluded from the study. Patients will be randomized after inclusion to one of four groups. The randomization is carried out to generate hypothesis for the needed dose and best time of application in the future. Triamcinolone acetonide will then be applied 20-24h before surgery or at the beginning of the surgery, depending on randomization (see below). About 20 µl of perilymph will be sampled simultaneously to a

blood sample during cochlear implant surgery. The first twenty patients will be randomized to Triamcinolone acetonide 40mg to allow for a first analysis of the samples. Patients 21 to forty will be randomized to Triamcinolone acetonide 10mg.

The probes will be stored at -80°C. Triamcinolone acetonide levels of the blood and perilymph will be determined by the pharmaceutical laboratory (Department of Pharmaceutical Technology and Biopharmaceutics, University of Vienna).

The patients will be randomized to 4 groups. Group 1 - Volon A® 10mg administration 20 - 24 hours before sampling. Group 2 – Volon® A 40mg administration 20 - 24 hours before sampling. Group 3 Volon® A 10mg – administration 1 to 2 hours before sampling. Group 4 – Volon A® 40mg administration 1 to 2 hours before sampling.

The time interval of application (1 to 2 hours and 20 to 24 hours before sampling) are a result of varying time of surgery depending on surgeons and patient anatomy as well as day to day clinical organization. Patients can withdraw consent at any time of the study.

The active phase of each patient will be between 6 and 9 days depending on time of follow-up visit.

[figure not shown]

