#### **8.5.3 End-of-study (EOS) examination**

One week after surgery patients routinely are scheduled for wound examination and stitch removal as well as scheduling of cochlear implant fitting. During this examination adverse events will be evaluated. Additionally, ear microscopy is carried out.

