## **10. FOLLOW-UP**

### **Follow-up of study participants including follow-up of adverse events**

Patients will be at the hospital at least two days after surgery (surgery = day 1). During this time patients will be asked for any adverse events on a daily basis. Additionally, patients will be followed up one week after surgery for wound inspection and stitch removal. At this follow-up visit patients will be asked for adverse events as well.

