## **Analysis sets**

### **Intention to treat set**

This analysis set includes subjects who were randomized (and received at least one dose study drug).

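### A patient dosed on day 0, then withdrawn and not operated on, has no planned adverse-event contact after the application visit; separately, the stated active phase and the last-visit window differ by one day

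*Protocol*

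**What the plan says.** **Follow-up after withdrawal.** Section 7.1.6 of the protocol lets subjects stop at any time. Its paragraph on the follow-up of withdrawn patients provides for one thing and rules out others: "Patients will be asked for adverse events at routine post-operative follow-up visits. No further follow up visits are necessary or planned within this study."

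**Other follow-up text.** Section 10 sets surgery as day 1 and describes daily questioning during the hospital stay after it. It continues: "Additionally, patients will be followed up one week after surgery for wound inspection and stitch removal." Section 8.5.3 anchors the end-of-study examination the same way: "One week after surgery patients routinely are scheduled for wound examination and stitch removal."

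**Timing of the drug.** Section 7 states: "Triamcinolone acetonide will then be applied 20-24h before surgery or at the beginning of the surgery", depending on the allocated group. Table 1 puts the application on day 0 for Groups 1 and 2 and on day 1 for Groups 3 and 4.

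**Table 1.** Adverse events are marked at visit 3 (application), visit 4 (day 1), visit 5 (day 2), visit 6 (day 3) and visit 7 (1 week, ±2 days).

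**Length of participation.** Section 7 says: "The active phase of each patient will be between 6 and 9 days depending on time of follow-up visit." The synopsis and section 7.1.5 give a maximum of nine days.

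**The concern.** In Groups 1 and 2 about a day passes between the injection and surgery, and a patient can leave the study in that interval. The rule for such patients relies on visits that exist only if surgery takes place. If it does not, the text provides no further question about adverse events, although the patient has received the study drug. The study rationale describes that drug as a crystalline compound with a presumed depot effect, used off-label by this route.

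The stake is completeness of safety information. Section 9.1.2 defines adverse events over the whole course of the study, and section 7.1.7 makes serious adverse events a ground for stopping the trial. Both call for information on every dosed patient. Someone who stops between injection and surgery may be someone who did not tolerate the injection, so a gap at this point is an awkward one.

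A smaller matter is that the day of the last visit and the stated length of participation do not agree. A visit inside the Table 1 window can therefore fall outside the stated participation.

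**Working it through.** **1. Which adverse-event contacts remain, by what happens after dosing on day 0 (Groups 1 and 2)**

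| Course after dosing | Contact at application (Table 1, visit 3) | Later contact provided in the text |
|---|---|---|
| Stays in study, operated on | yes | yes: hospital stay and one-week visit (sections 8.5.3 and 10) |
| Withdrawn, still operated on | yes | yes: post-operative visits (section 7.1.6) |
| Withdrawn, not operated on | yes | none: no post-operative visit exists and section 7.1.6 plans no other |

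Only the last row has a gap. For that patient, Table 1 lists checks on days 1, 2, 3 and at one week, while section 7.1.6 plans no visit at which they could be made. In Groups 3 and 4 the drug is given at the beginning of surgery, so the interval in which this could arise is practically absent.

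**2. How many patients**

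Inputs: 10 patients per group (synopsis), with Groups 1 and 2 dosed on day 0, so 2 × 10 = 20 of the 40 in Groups 1 to 4. The protocol gives no rate of withdrawal without surgery. If that share is assumed to be 2 to 10%:

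- 20 × 0.02 = 0.4 patients
- 20 × 0.10 = 2 patients

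The synopsis also lists a Group 5 sampled 24 h after administration. Patients in that group would add to the 20.

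**3. Length of the active phase**

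Inputs: surgery = day 1 (section 10); last visit one week after surgery (sections 8.5.3 and 10); window ±2 days (Table 1); inclusion on day 0 (section 8.5.2). The last visit falls on (anchor day + 7) ± 2, and elapsed time is that day minus the start day.

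The stated figure to reproduce is 6 to 9 days.

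| Start | Week counted from | Last visit on | Elapsed days | Days counted inclusively |
|---|---|---|---|---|
| day 0 | surgery, day 1 | day 6 to 10 | 6 to 10 | 7 to 11 |
| day 0 | day 0 | day 5 to 9 | 5 to 9 | 6 to 10 |
| day 1 (application, Groups 3 and 4) | surgery, day 1 | day 6 to 10 | 5 to 9 | 6 to 10 |

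None of these gives 6 to 9. The reason is simple: a ±2-day window spans 4 days (10 − 6), whereas 6 to 9 spans 3. On the text's own anchor (surgery on day 1, counted from day 0) the result is 6 to 10, which exceeds the stated maximum by 10 − 9 = 1 day. Section 8.5.1 accepts the flow-chart margins, so a visit on day 10 is admissible under one part of the protocol and beyond the stated participation under another.

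**The case against.** The strongest reply is that the protocol covers more than its follow-up paragraphs suggest.

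- **Table 1 is laid out by study day** and marks adverse events from the application visit onward. A reader might infer that all adverse-event follow-up hangs on surgery. The documents do not support that: visit 3 precedes surgery in exactly these groups, and nothing in the table makes visits 5 to 7 conditional on an operation. This stands. But visit 3 is the day of dosing, and section 7.1.6 overrides the later visits for a withdrawn patient by planning none outside post-operative care.
- **Withdrawal does not cancel the implantation.** Withdrawn patients who are operated on keep the enquiry, and a patient whose surgery is only postponed has post-operative visits later. This stands and narrows the gap to patients who are withdrawn and not operated on. Nor does section 7 show that postponement after dosing is expected; its remark on varying surgery times explains the width of the dosing-to-sampling intervals.
- **A reaction that causes withdrawal would be recorded.** Section 7.1.6 requires the reason for withdrawal in the CRF and the medical records, and section 12.1.1 requires a CRF for every enrolled subject. This stands. What could be missed is an event that appears later.
- **No analysis is biased.** A reader might infer that an adverse-event rate would be biased downward. The synopsis lists safety endpoints as not applicable, and section 11 plans no such rate. The inference fails; the loss is in safety reporting.
- **The day count is editorial.** The nine-day maximum is reproduced if the week runs from day 0, or from application in Groups 3 and 4, and the start of the active phase is not defined. This is partly right: the mismatch is one day and touches no endpoint. But sections 8.5.3 and 10 both count from surgery, and no reading tested returns 6 to 9.

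**Conclusion.** The point holds in a narrow form. After the application visit, the follow-up text places every adverse-event contact after surgery, and section 7.1.6 plans nothing else for withdrawn patients. A Group 1 or 2 patient who is dosed, withdrawn and not operated on therefore has no planned contact on the days that Table 1 lists.

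The size is small: 0.4 to 2 of 20 patients, resting wholly on the assumed 2 to 10%. No planned endpoint is affected. The consequence is incomplete safety data on a few dosed patients, mainly for events that begin after they leave. It is worth correcting because the remedy is so cheap.

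The contradiction in length does not depend on any assumed rate but is minor: day 6 to 10 from the visit schedule, against 6 to 9 days, and at most 9, in the text.

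**What to change.** 1. Reconcile the withdrawal paragraph of section 7.1.6 with Table 1, so that every dosed patient, operated on or not, is asked about adverse events on the days Table 1 already lists. Where there is no visit, this can be done by telephone. Except patients who withdraw consent to contact.
2. Reconcile the synopsis, sections 7, 7.1.5, 8.5.3 and 10 and Table 1 to one reference day and one window for the last visit, and state when the active phase begins. Which day count is intended is for the sponsor to decide.

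The cost is a few sentences in the protocol and at most a few telephone calls. Sampling, sample size and the planned analysis are unchanged.
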